### Retention Strategies

Participant retention is critical in all randomized controlled trials and may be even more important in open-label trials where differential attrition of study participants can occur and severely compromise the study results. Several strategies derived from a meta-analysis and expert recommendations have been put in place in order to improve the retention of study participants in this trial (79, 80) including thorough counseling of potential participants before enrolment, creation of a strong study brand, use of technology to ease the burden of participation (research calendar embedded in the mobile application, online dietary recalls with the R24W, email recalls), and flexible hours for study visits. Complementary healthy snacks and drinks will be offered at each study visit and parking fees will be assumed by the research team. After each research visit, participants will gain access to a new video through the mobile application, which will serve as a non-financial participation incentive. These videos have been created in collaboration with a local research team and provide scientifically accurate information on various aspects of parenthood. A fertility planner has been integrated in the mobile application as another non-financial participation incentive. Monetary compensations for time or travel will not be provided for this trial.

### Safety Monitoring

In order to document the safety of the *Healthy for my Baby* intervention, we have chosen to follow expert recommendations (81, 82) and implement a comprehensive adverse event monitoring strategy. Monitored adverse events include subjective anxious or depressive symptoms, a score of 8 or higher on the anxiety or depression subscale of the HADS questionnaire (68), physical trauma related to an increase in physical activity, placental abruption secondary to a trauma incurred in the context of an increase in physical activity, excessive weight loss on the part of the woman defined as the loss of more than 1 kg per week, intrauterine growth restriction associated with excessive maternal weight loss. These adverse events were defined based on plausible consequences of the intervention because no specific adverse events have been reported in association with lifestyle weight loss interventions (83). All adverse events will be reported to the DSMB, which will meet every 6 months or more often if needed, to evaluate the nature and rate of adverse events and determine their association with the intervention. If a severe adverse event occurs (requiring hospitalization, causing long-term morbidity, or death) the DSMB and local ethics board will be immediately notified to evaluate the need for trial interruption. No study termination criteria have been defined a priori.

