### Interventions

#### Intervention Arm

Participants randomized to the intervention group will receive the *Healthy for my Baby* intervention. This intervention is based on the Control Theory, according to which behavior can be regulated by engaging oneself in an active process centered on establishing and following-up specific goals (51). Couples will initiate the preconception intervention by participating in a 60-min motivational interview (MI) session on healthy lifestyle habits (52). At the end of this session, each member of the couple will have set specific SMART lifestyle goals (53) in at least two of five key areas: nutrition, physical activity, sleep, well-being (stress, anxiety), and environment (tobacco use, drug use, alcohol consumption, or other toxic substances). Lifestyle goals will be tailored to each participant based on the priorities verbalized in the motivational interview with the aim of improving compliance with Canadian guidelines for diet, physical activity, sleep, and consumption of alcohol (54, 55). Participants will then have access to a mobile phone application designed by our research team that will help them achieve three goals in different dimensions at a time through daily self-monitoring (Supplementary Figure 1). Self-monitoring has been shown in a meta-regression analysis to be the most effective behavior change strategy to improve diet and physical activity (56). In addition to allowing participants to track their lifestyle goals, the mobile application includes references on healthy habits for preconception and pregnancy, a research visit calendar, a fertility tracker, links to videos on different aspects of parenthood, and a platform to contact the research team.

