One month after enrolment, couples will participate in a second 30-min MI to reevaluate their objectives and help resolve potential obstacles. They will also be invited to set new SMART goals in three of the five key areas. Participants will continue to have access to the mobile application for the remainder of the preconception follow-up. The research team will have access to the information entered in the mobile application and will use this data to determine if the intensity of the intervention needs to be increased. Participants who successfully reach their lifestyle goals will not have any further in-person meetings in the preconception period. Those who fail to meet their lifestyle goals will be contacted for further support and will be invited to participate to a maximum of two additional monthly motivational interview sessions by videoconference. Participants will have the option to track their weight in the mobile application and will be contacted for further support if weight gain is reported. Several reminders have been embedded in the application to improve adherence to the intervention. The research team will also be able to detect participants who are not using the application on a regular basis to contact them for further support.

If the woman becomes pregnant, the application will be put in pregnancy mode and participants will be invited to engage in two additional 30-min MI sessions at 6–8 and 10–12 weeks of gestation. The aim of these additional encounters is both to intensify the intervention in the critical period of early pregnancy and to tailor the lifestyle goals to the symptoms of pregnancy. Participants will keep using the mobile application for self-monitoring throughout pregnancy and up to three additional monthly videoconference meetings will be planned for those requiring further support according to data derived from the application.

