##### Anxious and Depressive Symptoms

The intensity of anxious and depressive symptoms will be evaluated at each research visit with the *Hospital Anxiety and Depression Scale* (HADS). Both the anxiety (HADS-A) and depression (HADS-D) dimensions of this scale have been extensively validated in the general (67) and gynecological population (68). This questionnaire can also be utilized as a screening tool for anxious and depressive disorders with a cut-off value of 8 or greater on the HADS-A or HADS-D subscales (67, 68).

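### Subjective anxious or depressive symptoms count as adverse events with no stated common collection schedule, while only the intervention arm has extra sessions where they may come up, so the event rate is open to differential ascertainment.

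*Protocol article*

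**What the plan says.** **The event.** Safety Monitoring opens its list with "Monitored adverse events include subjective anxious or depressive symptoms". The next item is "a score of 8 or higher on the anxiety or depression subscale of the HADS questionnaire", so the subjective symptoms are an event in their own right and do not depend on the questionnaire. Every adverse event goes to the DSMB, which meets at least every 6 months "to evaluate the nature and rate of adverse events and determine their association with the intervention". No termination criteria are set in advance.

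**The shared schedule.** Under Anxious and Depressive Symptoms: "The intensity of anxious and depressive symptoms will be evaluated at each research visit with the" HADS. Table 1 gives a single schedule for both arms: baseline, 3 and 6 months in preconception, then 6–8, 24–26 and 32–34 weeks of pregnancy. No such schedule is stated for the subjective item.

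**The extra sessions.** Under Intervention Arm: "Couples will initiate the preconception intervention by participating in a 60-min motivational interview (MI) session on healthy lifestyle habits". Goals are set in at least two of five areas: "nutrition, physical activity, sleep, well-being (stress, anxiety), and environment". A second interview follows at one month. Participants who miss their goals "will be invited to participate to a maximum of two additional monthly motivational interview sessions by videoconference". After conception there are "two additional 30-min MI sessions at 6–8 and 10–12 weeks of gestation", and up to three more monthly videoconferences for those who need support.

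**The control arm.** Under Control Arm, participants have usual care and a simplified application. It keeps the platform for contacting the research team, which the full application also has. There are no interview sessions. Trial Design and Setting says that neither participants nor staff can be masked.

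**The concern.** A self-reported symptom enters the record only when there is an occasion to mention it and someone to note it. Both arms share the research visits. The intervention arm has further meetings with staff, and the topic of some of them may be the very symptom that counts as an event. The optional sessions go to participants who are not reaching their goals, so the extra contact is not spread evenly within the arm either.

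The DSMB has no preset threshold and reads the event rate to judge causation. If the intervention arm shows more subjective anxiety or low mood, the board could take an effect of the contact schedule for harm. It could equally dismiss a true excess as an effect of that schedule. With 68 women randomised 1:1, or 34 per arm, a handful of reports would be enough to create this difficulty.

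**Working it through.** The plan gives no symptom rate and no expected number of these events, so there is no figure of its own to reproduce. What can be checked is the number of staff contacts after randomisation. Online dietary recalls are left out because they are not meetings. So are the support contacts triggered by application data, because their number is not fixed. The counts are for a participant who completes the phase.

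**Inputs**
- Shared research visits (Variables and Data Collection; Table 1): 2 in preconception (3 and 6 months) and 3 in pregnancy (6–8, 24–26 and 32–34 weeks).
- Intervention-only sessions (Intervention Arm): in preconception 2 planned (start, 1 month) plus 0 to 2 optional; in pregnancy 2 planned (6–8 and 10–12 weeks) plus 0 to 3 optional.

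**Contacts and ratios.** Ratio = (shared visits + sessions) / shared visits. This equals the ratio of report rates only if reports are proportional to contacts and true symptom rates are equal. Both are assumptions.

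| Phase and count | Control | Intervention | Ratio |
|---|---|---|---|
| Preconception, all sessions | 2 | 2+2 = 4 to 2+4 = 6 | 4/2 = 2.0 to 6/2 = 3.0 |
| Preconception, without the first session | 2 | 2+1 = 3 to 2+3 = 5 | 3/2 = 1.5 to 5/2 = 2.5 |
| Pregnancy, all sessions | 3 | 3+2 = 5 to 3+5 = 8 | 5/3 = 1.7 to 8/3 = 2.7 |
| Pregnancy, 6–8 week session merged with the visit | 3 | 3+1 = 4 to 3+4 = 7 | 4/3 = 1.3 to 7/3 = 2.3 |

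The second row is there because the first session opens the intervention after the baseline assessment and may add little new reporting time. The fourth is there because the 6–8 week session and a shared research visit fall in the same window.

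**Participants with at least one report.** Let p be the chance of a report at any contact, equal in both arms (no true harm). Then P = 1 − (1 − p)^k for k contacts. In preconception, k = 2 in control and 4 to 6 in intervention:
- p = 1%: 2.0% against 3.9% to 5.9%
- p = 5%: 9.8% against 18.5% to 26.5%
- p = 10%: 19.0% against 34.4% to 46.9%

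At p = 5%, among 34 women per arm, that is about 3.3 against 6.3 to 9.0 women.

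**If sessions yield fewer reports than visits.** Let a session yield a report with probability s·p. For m sessions, P = 1 − (1 − p)^2 (1 − s·p)^m. At p = 5% and m = 2 to 4:
- s = 0: 9.8%, the same as control
- s = 0.2: 11.5% to 13.3%
- s = 0.4: 13.3% to 16.8%

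So the excess runs from zero upwards, depending on whether and how often session remarks become recorded events. The values of p and s are assumptions; the documents give neither.

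**The case against.** The strongest reply is that the link from session to event record is not in the text. A reader might infer that interviewers ask about symptoms, that remarks made in a session are logged as adverse events, and that the intervention arm will therefore report more. No section says so. The sessions set goals from the participant's own priorities, and well-being is one area of five that need not be chosen. Nor are controls left unasked: they attend the same research visits, complete HADS there, and can write to the team through the application. A real gain in well-being could also offset any extra reporting. All of this stands, and it rules out predicting an excess.

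Second, HADS already gives a check with equal ascertainment. It is a between-arm outcome at 3 and 6 months and continues through pregnancy, and a score of 8 or higher is itself a monitored event. The inference that nothing could later separate artefact from harm therefore goes too far. This also stands, and the remedy makes use of it. It does not settle the matter, because the subjective item is a separate event and no rule ties its interpretation to HADS.

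Third, an article may leave the method of eliciting events to the full protocol, and no formal between-arm test of adverse events is described. That is a fair limit, and if the full protocol has a safeguard the sponsor need only confirm it. But the vulnerability comes from what is stated: a subjective event, all events sent to the board, a causal judgement that uses their rate, and sessions in one arm only.

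**Conclusion.** The concern holds in a limited form. The subjective anxiety and depression item is open to differential ascertainment, and an intervention-arm excess in it could not be read with confidence as harm or as artefact. The documents do not show that such an excess will occur.

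The imbalance in contacts is a matter of count. The ratios in report rates are illustrations that rest on proportionality to contacts and equal true symptom rates, neither of which the documents support or refute. The true size is unknown.

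The point is confined to this item. It does not extend to HADS of 8 or higher, whose schedule is the same in both arms, or to adverse events as a whole. It does not touch the primary outcome or the sample size.

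**What to change.** In Safety Monitoring, state that the between-arm comparison of anxious or depressive adverse events rests on two sources only:
- HADS of 8 or higher, on the existing schedule.
- Symptoms elicited by one identically worded question at the research visits both arms attend: 3 and 6 months in preconception, and 6–8, 24–26 and 32–34 weeks of pregnancy.

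Add a field to the adverse event form for the source of each report (research visit, interview session, application message, other). Send events first raised in a session to the DSMB in full, but list them separately from the comparative rate.

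The cost is one question at visits already planned and one field on a form. The source should be recorded as events arise, since it cannot be reliably reconstructed later. The small downside is that events raised only in sessions leave the comparative rate, though the DSMB still sees every one of them.

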### Trial Design and Setting

This study is a multicenter open label parallel group randomized controlled trial coordinated at the Research Centre of the Centre hospitalier universitaire de Sherbrooke (CR-CHUS) in Sherbrooke, Quebec, Canada. The Province of Quebec has a population of 8.5 million. In 2014 overweight and obesity rates were 27 and 15% for adult women and 41 and 18% for adult men, respectively (49). Participants will be recruited from the Sherbrooke and Quebec City regions. The obstetrical care of women from Sherbrooke and Quebec City is provided by general practitioners, midwives, and obstetricians in outpatient clinics. The CHUS is a regional tertiary care center where ~2,800 deliveries are performed annually. The CHU de Québec Université Laval is a regional tertiary center where ~7,500 deliveries are performed annually at two sites, the Centre Hospitalier de l'Université Laval and the Hôpital Saint-François d'Assise.

An explanatory design has been chosen to rigorously evaluate the potential benefits of the *Healthy for my Baby* intervention (50). Masking of the research team and participants to the intervention will not be possible given the nature of the study. Couples will be randomized to the intervention or control group in a 1:1 ratio. The randomization list was generated independently by the CRCHUS' biostatistics service using a computerized unstratified blocked randomization with blocks of random sizes 2–6. The group allocation sequence was sent directly to the mobile application programming team who input it into the mobile application software. The mobile application website is hosted on the PIERCE server, a secured research platform developed by the local CRED medical informatics working group. Once participants have provided written consent, completed the trial enrollment form, and completed baseline assessment, their mobile application profile will be created by the research assistant which will trigger randomization to a treatment group. Participants will receive the result of their group allocation by email with a link to install the appropriate version of the mobile application.

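### Three monitored harms are defined by a suspected pathway, so whether an event counts can differ by arm and the between-arm comparison of these three is open to bias.

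*Protocol article*

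**What the plan says.** The Safety Monitoring section of the protocol article lists the adverse events to be monitored, chosen as harms that the intervention could plausibly cause. Three carry a condition about how the event arose:

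- Injury: "physical trauma related to an increase in physical activity".
- Abruption: "placental abruption secondary to a trauma incurred in the context of an increase in physical activity".
- Growth restriction: "intrauterine growth restriction associated with excessive maternal weight loss".

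Two others carry no such condition: "a score of 8 or higher on the anxiety or depression subscale of the HADS questionnaire" and "excessive weight loss on the part of the woman defined as the loss of more than 1 kg per week".

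Every adverse event goes to the DSMB, which meets "to evaluate the nature and rate of adverse events and determine their association with the intervention". Severe events (hospitalisation, lasting morbidity or death) are notified at once on severity alone. No termination criteria are set in advance.

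On masking, Trial Design and Setting states: "Masking of the research team and participants to the intervention will not be possible given the nature of the study". Under Interventions, the intervention application offers daily self-monitoring of goals and optional weight tracking. The control version is limited to a visit calendar, a fertility tracker, videos and a contact platform.

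**The concern.** An adverse event definition should let the same clinical event count in the same way in both arms. Here a fracture, an abruption or a growth-restricted fetus meets the listed definition only if it is tied to more exercise or to rapid weight loss. Someone has to make that link, and study staff know the allocation. The information needed to make it is also richer in the intervention arm.

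At stake is the DSMB's view of these three harms. If the link is made more readily in the intervention arm, the board sees an excess that may not exist. If staff are slower to blame the intervention, a true excess shrinks or disappears. With no preset termination criteria, the board works from judgement, and that judgement is only as good as the counts it receives.

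**Working it through.** **The plan's own figure.** The article gives no expected safety rate, so there is nothing to reproduce for harms. The arm size used below comes from Sample Size Calculation, reading the 10% difference as 10 points on the 100-point score: n = 2 × (1.96 + 0.84)² × 13² / 10² = 26.5, so 27 per group. Allowing for 20% attrition, 27 / 0.8 = 33.75, so 34 per arm and 68 in total. Both agree with the article.

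**Where the filter can differ by arm.**

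1. *Activity.* Both arms complete the activity questionnaire and a 7-day Fitbit recording around research visits (Table 1). The definitions do not refer to those measures. Between visits, an increase in activity is documented only through the intervention application and its support contacts.
2. *Weight loss.* The threshold is more than 1 kg per week. Scheduled weights are at 0, 3 and 6 months, then at 6–8, 24–26 and 32–34 weeks (Table 1). Averaged over 3 months (about 13 weeks), the threshold needs a loss of more than 13 kg. Over the shortest possible gap between the last two pregnancy visits (26 to 32 weeks, so 6 weeks), it needs more than 6 kg. Faster, shorter losses are visible only in more frequent weights, and these are described only for the intervention application. So even if the growth-restriction wording is read as simple co-occurrence, its condition is easier to detect in one arm.

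**Effect on a ratio.** Let r_I and r_C be the true event rates, and a_I and a_C the proportions of events judged to meet the qualifier. Then

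counted ratio = (r_I / r_C) × (a_I / a_C).

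The comparison is undistorted when a_I = a_C.

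**Injury, illustration.** All inputs are assumptions: 34 women per arm and the same true rate in both arms, 10% to 30% (3.4 to 10.2 injuries per arm).

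| a_I / a_C | Counted at 10% | Counted at 30% | Counted ratio (true = 1) |
|---|---|---|---|
| 50% / 50% | 1.7 v 1.7 | 5.1 v 5.1 | 1.0 |
| 70% / 30% | 2.4 v 1.0 | 7.1 v 3.1 | 2.3 |
| 90% / 30% | 3.1 v 1.0 | 9.2 v 3.1 | 3.0 |

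Reversing the second row (30% / 70%) gives 0.3 / 0.7 = 0.43, so a true ratio of 2 would appear as 0.86. Bias can run either way.

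**Abruption and growth restriction.** These arise only in women who conceive. If 50% to 80% do (assumption), that is 17 to 27 per arm. With an assumed abruption risk of 0.5% to 2%, the expected count is 0.09 to 0.54 per arm, and the chance of at least one is 8% to 42%. For growth restriction, suppose 3 cases in each arm, with 2 of 3 linked to weight loss in the intervention arm and 0 of 3 in controls: the listed count is 2 v 0 when the truth is 3 v 3. If the truth is 4 v 1 and none is linked, it is 0 v 0.

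**The case against.** The strongest case on the other side has five parts, and much of it stands.

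- *No pre-filter is stated.* The list is open ("Monitored adverse events include subjective anxious or depressive symptoms"), every adverse event is to be reported, and no assessor is named. A reader might infer that unmasked staff must rule on relatedness before an event reaches the DSMB. The article does not say that, and adverse event forms may sit in the full protocol.
- *Two judgements are distinct.* The qualifiers refer to activity or weight loss, which can occur in either arm. Association with the intervention is left to the DSMB. This stands, but it is a reason to give the board unfiltered events.
- *Growth restriction is worded as association.* It can be applied without a causal call. This stands too, though the weight-loss condition remains unequally detectable.
- *Other data exist.* Severe events are notified on severity, which would catch hospitalised abruptions and injuries recognised as adverse events. Birthweight and gestational age at delivery are abstracted from records in both arms, so small size for gestational age can be derived. It would therefore be wrong to infer that no other route recovers these events, or that they are the board's main safety information. Still, neither abruption nor growth restriction is itself among the listed record-abstracted outcomes.
- *Small numbers dominate.* Complete counts of 4 v 1 among 17 to 27 pregnancies per arm would give a two-sided Fisher p of about 0.34 to 0.35. Rewording will not create power. Its purpose is to keep a small comparison from also being a biased one.

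The asymmetry should not be overstated either: goals are first set in at least two of five areas, so an activity goal is not compulsory, and no weight goal is listed.

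**Conclusion.** The definitions of physical trauma, placental abruption and intrauterine growth restriction depend on pathways that the intervention aims to change. In an unmasked trial with closer tracking in one arm, the between-arm comparison of these three events is open to bias in either direction.

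The conclusion rests on the stated wording plus one inference: that people who know the allocation would apply the qualifiers. The size is unknown. The illustrative ratios of 2.3 to 3.0 depend wholly on assumed attribution differences and vanish if attribution is equal.

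A reader might go further and conclude that the arms cannot be compared on safety. The documents do not support that. Anxiety and depression scores, weight-loss events and severe events need no attribution, and the three affected comparisons are exposed to bias rather than impossible. This is a worthwhile, inexpensive improvement and does not invalidate the safety plan.

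**What to change.** In Safety Monitoring:

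1. Remove the qualifiers from the three definitions, so that they read as physical trauma needing care, placental abruption, and diagnosed intrauterine growth restriction, each recorded whatever its presumed cause.
2. Collect them in the same way in both arms: the same question at each research visit, plus the medical record review already planned for the end of the study, with abruption and growth restriction added to the abstracted items.
3. Record presumed cause (including any link to activity or weight loss) as a separate field.
4. Report all such events by arm to the DSMB, which keeps the judgement on relatedness.

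The cost is a wording change, two or three extra fields, and some clearly unrelated events in the DSMB listings. Because recruitment has begun, the change also has to go to the ethics committees and the registry, as the article already requires for any amendment. Abruption and growth restriction in women already enrolled can be picked up at record review; earlier injuries can be asked about at the next visit.
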